#### The hospital anxiety and depression scale

This will be used to evaluate the depression and anxiety of chronic migraine patients (Zigmond and Snaith, 1983). Cut-off points are ≥ 10 and ≥ 13 for depression and anxiety, respectively.

#### Epworth sleepiness scale

The study participant’s daytime sleepiness will be measured with ESS (Johns, 1991).

#### Pittsburgh sleep quality questionnaire

This records the sleep status of the past month, including the following six sub-items: sleep quality, sleep onset time, sleep hours, sleep efficiency, sleep disturbance, use of sleep medication, and daytime activity. It will be filled in by self-assessment, with a total score of > 5 indicating poor sleep quality (Buysse et al., 1989).

#### General sleep disturbance scale

This questionnaire utilizes a weekly sleep rating scale of 0–7, which includes 21 items related to frequency, in the past week, quality of sleep, quantity of sleep, fatigue and wakefulness at work, and use of sleep-promoting substances (Lee, 1992; Lee and DeJoseph, 1992; Lee, 2007).

#### Wrist actigraphy (Mini Motionlogger Actigraphy, AMI, Ardsley, NY)

A lightweight watch-lime motion sensor monitor will be used to collect objective sleep data, including total nocturnal and day sleep time (TST), WASO, and circadian activity rhythms for 7 consecutive days. Various investigators in the past have demonstrated a very high correlation (*r* = 0.93–0.99) between the two measures of total sleep time during the night and measures of wakefulness using the sleep polysomnography (PSG) (Jean-Louis et al., 1996; Ancoli-Israel et al., 1997).

#### Polysomnography

In addition to the wrist actigraphy data, an overnight sleep visit will be required to collect the objective sleep data.

#### Physiological indicators

A blood sample will be collected to measure CGRP and PACAP.

### Data management

The following information will be obtained from each subject: demographics, 4-week headache data (pre and posttreatment), pre and posttreatment outcome variables (PGI-I, PGI-S, MIDAS, HADS, PSQI, and GSDS), selected physiological indicators (PSG, CGRP, and PACAP), and pre and posttreatment 7-day wrist actigraphy data (TST, WASO, circadian activity rhythm). The physiological analysis will be performed in the hospital’s laboratory using established laboratory protocols for specimen processing and analysis. Assay preparation will be performed following the manufacturer’s instructions. The sleep data obtained with the watch will be analyzed by using the Action 4 software, and the PSG will be analyzed by using the Crystal software.

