#### Detection of headache-related scales

Patient Global Impression of Improvement (PGI-I) is an assessment to measure disease improvement (Guy, 1993). PGI of Severity (PGI-S) will be used to measure the severity of migraine (Guy, 1993). The Migraine Disability Assessment (MIDAS) (Stewart et al., 1999) will be used to assess migraine-related disabilities in different areas of life in the past 3 months.

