### Data analysis

All data analyzes will be conducted using the intent-to-treat principle. When considering the results of multiple comparisons, the Bonferroni correction will be used to correct the significance level. Pre and posttest, the related scales of the experimental and control groups, such as the headache diary, PGI-I, PGI-S, MIDAS, HADS, PSQI, ESS, GSDS, and PSG, wrist actigraphy, and blood test analysis, will be expressed as mean ± standard deviation.

The above-mentioned scales and blood test values of the pre and posttreatment assessments of each patient will be tested with the Sign test to identify any difference before and after the test. Finally, the generalized estimating equation model will be used to evaluate whether the experimental group significantly had reduced pain frequency and severity and improved sleep than the control group to understand the effect of light therapy on migraine.

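### PGI-I rates improvement, yet it is scheduled at pretest and put through the pre/post Sign test with no reference point for a pretest rating

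*Protocol article*

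**What the plan says.** Four places in the protocol article bear on this.

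- **Detection of headache-related scales** says what the two global ratings are for: "Patient Global Impression of Improvement (PGI-I) is an assessment to measure disease improvement", whereas "PGI of Severity (PGI-S) will be used to measure the severity of migraine".
- **Table 1 (Data collection)** marks PGI-I at Pretest and at the 4th week, the same pattern as PGI-S.
- **Data management** lists it first among the "pre and posttreatment outcome variables (PGI-I, PGI-S, MIDAS, HADS, PSQI, and GSDS".
- **Data analysis** opens its list of measures with "Pre and posttest, the related scales of the experimental and control groups, such as the headache diary, PGI-I", to be summarised as mean and standard deviation. The next paragraph takes those scales and the blood values and says the pre and post assessments of each patient "will be tested with the Sign test to identify any difference before and after the test".

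The only between-group model is described separately: "the generalized estimating equation model will be used to evaluate whether the experimental group significantly had reduced pain frequency and severity and improved sleep". PGI-I is not named there.

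**The concern.** The article itself separates a rating of change (PGI-I, improvement) from a rating of state (PGI-S, severity), and then handles both as states measured twice. A severity rating has a natural value before treatment. An improvement rating has one only relative to an earlier time, and the article gives none. Pairing a pretest PGI-I with a posttest PGI-I therefore either adds no information or compares two different quantities.

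At stake is whether the PGI-I result can be interpreted. A global impression of improvement can be a useful patient-reported summary when the arms are compared on it after treatment. As written, the one test attached to it compares each woman with herself through a pretest value that has no defined meaning.

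**Working it through.** The article states no figure that depends on this point, so no arithmetic applies. The check traces PGI-I through the text and then asks what the planned difference would measure.

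**Step 1: is it a slip in one place?** No. The Table 1 schedule, the Data management list and the Data analysis list all treat PGI-I as a pre/post measure. No sentence exempts it from the Sign test or supplies a reference period.

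**Step 2: what does the Sign test need?** It takes, for each woman, the sign of (post value minus pre value), so the two values must be of the same quantity. Write S for a woman's migraine severity, with higher values worse. PGI-S records S at pretest and S at week 4, and their difference is the change in severity. PGI-I at week 4 is already a rating of such a change, roughly S(pretest) minus S(week 4).

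**Step 3: what could the pretest PGI-I be?**

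- *Case A: every woman rates no change at pretest.* The pretest value is a constant c. The sign of (week-4 rating minus c) is then simply whether the week-4 rating lies above or below no change. The test is a one-sample test of the week-4 rating, and the pretest column contributes nothing.
- *Case B: women rate change over some earlier period.* The pretest rating is roughly S(earlier) minus S(pretest). Week-4 minus pretest is then [S(pretest) − S(week 4)] − [S(earlier) − S(pretest)], a difference of two changes with different anchors. A woman who improved before enrolment and improved equally during treatment scores zero, the same as a woman who never changed. A woman who was worsening before enrolment and then merely held steady scores as a gain.

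**Step 4: does either case measure the light effect?** No. Case A asks whether women feel better at week 4. Case B asks whether the rate of change differs between two periods, one of them undefined. Neither contrasts green light with red light.

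**Step 5: how far does it reach?** The Objectives name sleep variables, migraine frequency and severity, and quality of life. The GEE sentence names pain frequency and severity, and sleep. PGI-I appears in neither.

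**The case against.** The best defence is that the article says only that PGI-I measures improvement. It does not spell out improvement since the start of treatment, and a condensed article may leave rating instructions to the full protocol. The abstract describes a 4-week monitoring period before treatment, so a pretest rating could refer to change over that interval, and the paired comparison would then set change on treatment against change before it. This is possible, but nothing says so. Table 1 does not show whether the single pretest rating falls at the start or the end of monitoring, and the result would still be Case B. Had both ratings been tied to one common earlier date, the difference would be coherent, but it would amount to a change in state, which PGI-S already provides. The problem is also not a missing detail: the article affirmatively schedules, lists and tests PGI-I as pre/post.

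Several stronger readings are tempting and are not supported.

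- *The PGI-I test is wholly meaningless.* Under Case A it is still an interpretable one-sample test. It is redundant in its pretest part, and it is not a test of the light.
- *The PGI-I test will produce a false claim for the light at some given rate.* The article gives no response rate, handling of ties or number of tests from which to compute one. It says only that "the Bonferroni correction will be used to correct the significance level", without defining the family, so no argument about wasted significance level can be built on PGI-I either.
- *The trouble is placebo response.* Improvement from sleep hygiene education or expectation does enter a within-patient Sign test, but that is true of every scale listed and is not special to PGI-I.
- *No between-arm use of PGI-I is foreseen.* The ratings are to be summarised for both groups, so week-4 values by arm will be visible. A formal between-arm test is not named, which in a condensed article is not an error in itself.

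**Conclusion.** The point holds in limited form. By the article's own description PGI-I is a rating of change, and three places treat it as a state measured before and after treatment, with no reference point for the pretest value. The planned pre/post difference is a redundant one-sample test under one reading and a difference of ratings with different anchors under the other. Neither estimates the effect of light therapy.

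This rests on reading improvement as change from an earlier time, which follows from the scale's name and stated purpose and from the contrast with PGI-S. It does not rest on any assumed response rate.

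The size is small: one scale outside the Objectives and the GEE comparison. The sample size and the between-group analyses of headache and sleep do not depend on it. It is still worth correcting, because the text is wrong as written and the repair is nearly free.

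**What to change.** 1. In Table 1, delete the pretest mark for PGI-I and keep the 4th-week mark.
2. In Data management, take PGI-I out of the pre and post list and describe it as a posttreatment outcome.
3. State the reference point for the week-4 rating: compared with before the start of the intervention.
4. In Data analysis, exclude PGI-I from the Sign test and from the pretest summaries. Compare the week-4 ratings between arms as an ordinal outcome, either by a rank-sum test or by a proportional-odds model. If adjustment for baseline PGI-S is wanted, use the proportional-odds model; a plain rank-sum test cannot adjust.
5. Keep PGI-S at both times as the pre/post global scale.

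The cost is one table cell and a few sentences, with one questionnaire fewer for participants at pretest. If pretest ratings have already been collected, they can be left out of the analysis and the week-4 comparison made as above, provided the reference point actually used at week 4 is reported.

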### Data analysis

All data analyzes will be conducted using the intent-to-treat principle. When considering the results of multiple comparisons, the Bonferroni correction will be used to correct the significance level. Pre and posttest, the related scales of the experimental and control groups, such as the headache diary, PGI-I, PGI-S, MIDAS, HADS, PSQI, ESS, GSDS, and PSG, wrist actigraphy, and blood test analysis, will be expressed as mean ± standard deviation.

The above-mentioned scales and blood test values of the pre and posttreatment assessments of each patient will be tested with the Sign test to identify any difference before and after the test. Finally, the generalized estimating equation model will be used to evaluate whether the experimental group significantly had reduced pain frequency and severity and improved sleep than the control group to understand the effect of light therapy on migraine.

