### Objectives

The specific goals of this prospective study are to (1) compare the effects of BLT (green light and sleep hygiene) with an attention control treatment (placebo light and sleep hygiene) on selected sleep variables [total nocturnal sleep time, wake after sleep onset (WASO), sleep efficiency, daytime sleepiness], migraine conditions (frequency and severity), and QOL (mental health) from baseline to 1 month after beginning the intervention; and (2) explore the light therapy’s molecular and biochemical effects on migraine prevention.

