### Inclusion and exclusion criteria

The inclusion criteria are as follows: diagnosed with migraine according to the International Classification of Headache Disorder 3rd edition (ICHD-3); aged 20–65 years; with sleep disorders (PSQI >5 points); willing to participate in activity monitoring (wrist recorder) during the day and night for 9 consecutive weeks, and one night in the sleep room for polysomnography, totaling to two time periods (before and after treatment); willingness to have blood drawn twice; not allergic to metals (a contraindication to wearing wrist actigraph); and not currently participating in other interventional trials.

The exclusion criteria are as follows: non-migraine headaches (e.g., tension-type or secondary headaches, among others); major head trauma in the past; alcoholism within 1 year; (4) pregnant or breastfeeding women; (5) cannot cooperate with the test progress; (6) allergic to light; and (7) taking beta-blockers, antiepileptic drugs, calcium ion blockers, antidepressants, onabotulinumtoxinA, CGRP monoclonal antibody, and hormone preparations in the past month.

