### Interventions

Our study has a two-component intervention package, including a 30-min daily BLT (green and red lights for the treatment and control groups, respectively) and a sleep hygiene educational package for 4 weeks. The bright light visor (Feel Bright Light Model 100, Physician Engineered Products, Fryeburg, ME) will be used for the treatment group; however, the visor delivers blue–green light, thus we blocked the blue light and remind the participants to use the green light to prevent potential damage to eyes, especially the elderly. The unit weighs approximately 1.7 ounces, is comfortable to wear, and is powered by a rechargeable battery, allowing participants to move freely for their daily work. Participants will undergo 30 min of BLT within an hour of waking up for 4 weeks. A red-light visor (Physician Engineered Products, Fryeburg, ME), an attention control strategy, that does not have any therapeutic effect will be used for the control group. Both groups will receive a sleep hygiene educational booklet.

Sleep hygiene is fundamental to improving sleep and is considered an important intervention to promote sleep (McCurry et al., 2004). Sleep B.E.T.T.E.R. will be included in this educational package. This booklet includes information on normal sleep and promoting the homeostatic drive for sleep using the following six basic guidelines: bedroom environment, regular daily exercise, reducing tension and stress, time trying to sleep, eating and drinking, and maintaining regular day–night rhythms.

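### HADS, MIDAS, CGRP and PACAP are given only a before/after Sign test, although the objectives ask about the effect of light and, for mental health, a comparison with the control light

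*Protocol article*

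**What the plan says.** The Data analysis section of the protocol article describes three layers.

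1. **Summary.** Each group gets a mean and a standard deviation for the listed measures, "such as the headache diary, PGI-I, PGI-S, MIDAS, HADS, PSQI, ESS, GSDS, and PSG, wrist actigraphy, and blood test analysis". This is description, not a test.
2. **Before/after test.** "The above-mentioned scales and blood test values of the pre and posttreatment assessments of each patient will be tested with the Sign test", and its purpose is "to identify any difference before and after the test". The section does not say whether this is run within each arm or over all women together.
3. **Between-arm model.** A GEE is used to "evaluate whether the experimental group significantly had reduced pain frequency and severity and improved sleep than the control group".

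The section also applies the intent-to-treat principle and a Bonferroni correction, without giving the number of tests.

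Under Objectives, the first aim compares green light with an attention control on sleep, migraine and quality of life (mental health). The second explores the light therapy's "molecular and biochemical effects on migraine prevention". Under Interventions, "Both groups will receive a sleep hygiene educational booklet".

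**The concern.** HADS, MIDAS, CGRP and PACAP appear in the first two layers but not in the third. HADS measures anxiety and depression and is the listed instrument that fits the mental-health part of objective 1. CGRP and PACAP are the blood measures that serve objective 2. MIDAS is the disability outcome.

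A before/after test asks whether scores moved over the month, not whether they moved because of green light. Anything that moves both arms, such as sleep hygiene education or the passage of time, counts as change. The trial randomises women to green or red light so that such shared change can be subtracted, and for these four outcomes the article states no test that does so. The risk is a report that light changed mood, disability or a neuropeptide when the randomised contrast was not examined. If the test is run in each arm, the familiar error is to read a significant change under green and a non-significant one under red as a difference between arms.

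**Working it through.** **Step 1. Match each outcome to its stated test (Data analysis section).**

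| Outcome | Before/after Sign test | Between-arm GEE |
|---|---|---|
| Headache diary (frequency, severity) | yes | yes, named |
| PSQI, ESS, GSDS, PSG, actigraphy | yes | yes, reasonably read under sleep |
| PGI-S | yes | arguably, under severity |
| HADS | yes | not named |
| MIDAS | yes | not named |
| CGRP, PACAP | yes | not named |

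**Step 2. Inputs for the size of the problem.**
- From the article (Study design): 30 women per arm, 60 in total. The article gives no alpha, SD or expected change, so there is no power figure to reproduce.
- Assumed: two-sided exact Sign test, no ties, normally distributed change scores, no light effect, and the same mean change in both arms of d = 0.3, 0.4 or 0.5 SD of the change score.
- Assumed for Bonferroni: 0.05/11 = 0.0045, taking the 11 listed measures as the number of tests.

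**Step 3. Critical values.** Find the smallest r with 2 × P(X ≥ r) ≤ alpha, where X is Binomial(n, 0.5).
- n = 30, alpha 0.05: r = 21 (actual size 0.043; r = 20 would give 0.099).
- n = 30, alpha 0.05/11: r = 24 (actual size 0.0014).
- n = 60, alpha 0.05: r = 39 (0.027).
- n = 60, alpha 0.05/11: r = 42 (0.0027).

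**Step 4. Chance of a significant improvement when light does nothing.** The probability that a woman improves is p = Φ(d), so the chance is P(X ≥ r) with X Binomial(n, p).

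| Shared change d | p | One arm of 30, 5% | One arm of 30, 0.05/11 | Pooled 60, 5% | Pooled 60, 0.05/11 |
|---|---|---|---|---|---|
| 0.3 | 0.618 | 23% | 3% | 36% | 12% |
| 0.4 | 0.655 | 38% | 7% | 59% | 28% |
| 0.5 | 0.691 | 55% | 14% | 80% | 51% |

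**Step 5. Green significant, red not, if the test is run per arm.** With q the one-arm probability from Step 4, this is q(1 − q).
- At 5%: 0.233 × 0.767 = 18%; 0.381 × 0.619 = 24%; 0.548 × 0.452 = 25%.
- At 0.05/11: 0.027 × 0.973 = 3%; 0.066 × 0.934 = 6%; 0.137 × 0.863 = 12%.

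The correction lowers the rates but does not remove the confounding: they rise with the shared change, because the Sign test correctly detects a change that is not due to light.

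**Step 6. What the between-arm contrast offers.** It would call equal change in both arms a light effect at about the nominal level. By the normal approximation, the difference detectable with 80% power at 30 per arm is (z for alpha/2 + 0.84) × √(2/30):
- at 0.05: (1.96 + 0.84) × 0.258 = 0.72 SD;
- at 0.05/11: (2.84 + 0.84) × 0.258 = 0.95 SD.

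At a true difference of 0.5 SD, power is 49% and 18% respectively. These outcomes will be estimated imprecisely, which is a reason to report the difference with its interval rather than a p-value alone.

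**The case against.** The strongest reply has four parts.

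*The main outcomes are already compared between arms.* This is correct. A reader might infer that all the scales are judged only by before/after change, but the GEE sentence reasonably covers the diary, PSQI, ESS, GSDS, PSG and actigraphy, and arguably PGI-S. Two tempting arguments also fall away. Regression to the mean from selecting women "with sleep disorders (PSQI >5 points") acts directly on PSQI, and getting used to the sleep laboratory acts on PSG; both are sleep outcomes that have the between-arm model. Of the built-in sources of shared change, sleep hygiene education is the one that carries over to the four outcomes, along with time itself.

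*The article never says it will infer a light effect from the Sign test.* This is also correct; it gives that role to the GEE. But it then names no GEE analysis for the four outcomes, so the Sign test is the only p-value that a reader of the results could attach to them.

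*The 5% figures ignore the stated Bonferroni correction, and the green-only figures assume per-arm testing.* Both points are fair. That is why both significance levels and the pooled alternative are shown. The Bonferroni divisor is itself an assumption.

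*Objective 2 is exploratory, and a condensed article may leave details to a fuller plan.* This limits the claim to what the article states. It does not dispose of it, because the article assigns these outcomes a test and that test does not address the stated question. An exploratory effect of light still calls for a comparison with the control light.

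**Conclusion.** The point holds for HADS, MIDAS, CGRP and PACAP and no further. Their only stated inferential test is uncontrolled, which does not match objective 1 for mental health or objective 2 for the biomarkers.

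The size depends on assumptions that the article cannot settle: a shared change of 0.3 to 0.5 SD, no ties, and per-arm testing. On those terms, one arm shows a significant improvement without any light effect in 23% to 55% of trials at 5%, or about 3% to 14% at 0.05/11. No shared change specific to CGRP or PACAP is documented, so for the blood markers the range is an illustration, not a forecast.

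The gap concerns wording and is easily closed. It does not undermine the planned comparison of headache and sleep outcomes.

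**What to change.** In the Data analysis section:

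1. Extend the between-arm GEE to HADS, MIDAS, CGRP and PACAP, either as group by time or as the posttest value adjusted for that outcome's baseline. Report the green-minus-red difference with a 95% CI.
2. Label the Sign test as descriptive, and say whether it is run by arm or pooled.
3. State that only the between-arm contrast supports a claim about light.

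The Sign test need not be deleted, nor the GEE replaced for the outcomes that it already covers.

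**Cost.** No new data: Table 1 already schedules all four measures before and after treatment, and the schedule is not split by arm. The analysis grows slightly, the Bonferroni correction must cover more comparisons, and the before/after p-values lose their inferential role.
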